### Presentation of results in tables

Tables 3, 4, 5 and 6 show how the results of the analysis of the primary outcome (Table 3), the binary secondary outcomes (Table 4), the continuous secondary outcome and exploratory outcomes (Table 5), and the SAE data (Table 6) will be presented.

**Table 3 Tab3:** Comparison of the distributions of the modified Rankin scale (mRS) between the two intervention groups in each analysis set (intention-to-treat or per protocol)

Population studied	Intervention group	mRS = 0	mRS = 1	mRS = 2	mRS = 3	mRS = 4	mRS = 5	mRS = 6	Common OR	P of difference
		N (%)	N (%)	N (%)	N (%)	N (%)	N (%)	N (%)	(95% CI)	(reference = group 0)
Intention-to-treat (ITT)	Group 0									
	Group 1									
Per protocol (PP)	Group 0									
	Group 1

**Table 4 Tab4:** Comparison of the distributions of the secondary binary outcomes between the two intervention groups in each analysis set (intention-to-treat and per protocol)

Population	Intervention group	Outcomes					
		Death			mRS > 2		
		N (%)	Relative risk (RR) (95% CI)	P	N (%)	RR (95% CI)	P
Intention-to-treat (ITT)	Group 0						
	Group 1						
Per protocol (PP)	Group 0						
	Group 1						

*mRS* modified Rankin score, *CI* confidence interval

**Table 5 Tab5:** Comparison of distributions of the secondary continuous outcomes between the two intervention groups in each analysis set (intention-to-treat or per protocol)

Outcome	Population	Intervention group	Percentiles			N	Mean (SD)	(Minimum, maximum)	*P* of difference
			25%	50%	75%				
NIHSS score Range of possible scores at 91+/-14 days (RS): 0 to 42 Worst = 42	Intention-to-treat (ITT)	Group 0							
		Group 1							
	Per protocol (PP)	Group 0							
		Group 1							
EQ-5D-5 L score at 91+/-14 days RS: 0 to 100 Worst = 0	ITT	Group 0							
		Group 1							
	PP	Group 0							
		Group 1							
Brain infarct size at 48 +/-24 hours Worst = 1	ITT	Group 0							
		Group 1							
	PP	Group 0							
		Group 1							
WHODAS 2.0 score at 91+/-14 days	ITT	Group 0							
		Group 1							
	PP	Group 0							
		Group 1							

*SD* standard deviation, *NIHSS* National Institutes of Health Stroke Score, *EQ-5D-5 L* EuroQoL quality-of-life scale

**Table 6 Tab6:** Amendments made relative to the original statistical analysis plan published in the protocol

Topic described in original statistical analysis plan	Handling of topic in the present amended statistical analysis plan	Reason for action
No adjustment for nationality.	Adjustment for nationality	To improve the power by preventing upward bias of the standard error of the outcome.
Power calculation of secondary outcomes is missing	Calculation of power conditional on sample size	To be used when defining the test ordering of the secondary outcomes
Difficulties involved in interpreting an effect on a secondary outcome that can only be measured in surviving patients was not addressed	The worst possible score is assigned to the dead patients	A surplus of patients in one group relative to the other group may die before the outcome is measured. In the other group the corresponding surviving patients may (or may not) have very poor outcomes
No multiplicity adjustment	The fixed-sequence testing procedure will be applied with the primary outcome to be tested first and followed by the secondary outcomes ordered according to falling power	To keep the family-wise error rate ≤ 0.05
A search for auxiliary variables and if found followed by imputation of the primary outcome was not considered	Missing value handling procedure revised accordingly	To improve the efficiency of a multiple imputation of missing values of the primary outcome
The analytic potential of the exploratory temperature data was not expanded on	An outline of an exploratory mixed model analyses of the temperature data and Cox analyses of time to death with censoring at end of treatment and at 91 days +/- 14 days is now included	To assess if the temperature has an impact on short-term and long-term mortality and supplement the result of the analysis of the second secondary outcome
Sample size of 1500 participants	Sample size reduced to 800 participants	Due to exceptionally slow enrolment, we realised that this target was no longer realistic

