#### Power of the original secondary outcomes

As the sample size is based on the primary outcome, we have calculated the power of each of the originally planned secondary outcomes given the sample size of 800 patients.

Death day 91 ± 14 days after randomisation: the implied clinically relevant minimal change in mortality that needs to be detected may be calculated based on (1) the mortality of 17% found in the meta-analysis quoted in the protocol [1]; (2) the assumption that wherever the mRS is dichotomised, the odds ratio for treatment versus control will be the same, the ‘common odds ratio’; and (3) the requirement that this common odds ratio should not be larger than 0.74 (see the sample size calculation). Let the unknown change in mortality in the experimental group be x. If we assume the OR for the dichotomy mRS > 5 compared to mRS ≤ 5 will be 0.74 and the mortality of the control group is 17% as quoted in the meta-analysis, we may find x by solving the equation OR = ((0.17–x)/(0.83 + x))/(0.17/0.83) = 0.74 to obtain x = 0.0384 giving a mortality of 0.1700 – 0.0384 = 0.1316 in the cooled patients versus 0.1700 in the controls. Using a sample size of 800 participants, the power is found to be 0.33.

Death or dependency (mRS > 2) 91 ± 14 days after randomisation: using the same reasoning, the power of this outcome can be calculated by solving the equation (0.63–x)/(0.37 + x))/0.63/0.37 = (0.63 – x)0.63/(0.37 + x)0.37 = 0.74 as 63% of the patients in the meta-analysis had mRS > 2 implying x = 0.0725. The power may then be calculated to be 0.55.

NIHSS score 91 ± 14 days after randomisation: assuming a minimal relevant difference of 2 points, a standard deviation (SD) of 5 points [5], an α of 0.05, and a sample size of 800 participants, the power may then be calculated to 1.00.

EQ-5D-5 L score 91 ± 14 days after randomisation: assuming a minimal relevant difference of 0.05 points, a SD of 0.40 points [6–9], an α of 0.05, and a sample size of 800 participants, the power may then be calculated to 0.42.

WHODAS 2.0 score 91 ± 14 days after randomisation: we originally planned to analyse the World Health Organization Disability Assessment Schedule II (WHODAS 2.0) score at outcome assessment in the period day 91 ± 14 days after randomisation. However, due to difficulties in assessing the clinical meaning, we are not able to calculate the power, and we will thus analyse this as an exploratory outcome.

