Brain infarct size 48 ± 24 hours after randomisation: assuming a minimal relevant difference of 2 ml, a SD of 15 ml [10], an α of 0.05, and a sample size of 250 participants, the power may then be calculated to 0.18. Accordingly, this outcome will be exploratory.

Number of patients with at least one serious adverse events 91 ± 14 days after randomisation: assuming a control group event proportion of 20% of patients with at least one SAE, an intervention group event proportion of 10% [11], an α of 0.05, and a sample size of 800 participants, the power may then be calculated to 0.98.

Mean number of SAEs per patients: As we do not have prior data to indicate a probable minimal relevant difference, we cannot calculate power for this outcome. These data will be analysed as an exploratory outcome.

The results of calculations of the power are all shown in Table 2. These results are used to determine the sequence in which the secondary outcomes should be tested using the fixed-sequence approach, i.e. the sequence will be as follows:Score on NIHSS at outcome assessment in the period day 91 ± 14 days after randomisation.Proportion of participants with at least one serious adverse event (SAE) until outcome assessment in the period day 91 ± 14 days after randomisation.Death or dependency, defined as a score on the mRS > 2 at outcome assessment in the period day 91 ± 14 days after randomisation.Brain infarct size at imaging assessment in the period 48 ± 24 hours after randomisation.EQ-5D-5 L score at outcome assessment in the period day 91 ± 14 days after randomisation.Death at outcome assessment in the period day 91 ± 14 days after randomisation.

The exploratory outcomes are:WHODAS 2.0 score at outcome assessment in the period day 91 ± 14 days after randomisation.Number of SAEs per patient until outcome assessment in the period day 91 ± 14 days after randomisation.

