### Overview of changes to the original statistical analysis plan for the primary and the secondary outcomes

Table 7 presents an overview of the changes relative to the original statistical analysis plan and explain the reasoning behind. The only substantial changes relative to the original plan includes that we now: (1) adjust the analyses by the protocol-specified stratification variable, i.e. nationality to improve the power [15]; (2) power calculations for secondary outcomes; (3) address the multiplicity problem by using a fixed-sequence procedure starting with the primary outcome followed by the secondary outcomes ordered according to falling power; (4) due to the low power involved in detecting small (1–5%) differences in mortality between the groups, assign worst possible score to patients who are not alive at the planned date of measurement of the continuous scores; (5) include auxiliary variables in the potential multiple imputation of missing value of the primary outcome to improve the efficiency of the imputation; and (6) outline a supplementary exploratory analysis of the temperature measurements and time to death; (7) substantial reduction of sample size.

**Table 7 Tab7:** Total number of serious adverse events (SAEs), and number of patients with at least one SAE groups in each analysis set (intention-to-treat or per protocol)

Types of events	Group 0			Group 1		
	Events, N	Patients with at least one event, N	Patients assessed, N	Events, N	Patients with at least one event, N	Patients assessed, N
Any event						
Event type 1						
Event type 2						
Event type 3						
Etc						

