### The interpretation of the effect on outcomes which may only be measured in surviving patients

Formally, three of the original secondary outcomes (NIHSS, EQ-5D-5 L, and infarct size) are only measurable in patients who survive until these outcomes were planned to be measured. This may make the interpretation of a significant effect on each of the last four secondary outcomes somewhat difficult when the power of detecting a small difference between the mortalities in the two groups is low. A surplus of patients in one intervention group relative to the other group may die before the outcome is measured. In the other intervention group, the corresponding surviving patients may (or may not) have very poor outcome values which may make the first group look good if the mortalities do not differ significantly.

Given the sample size of 800 patients and assuming the mortality in one group is 0.17 (e.g. in the control group, see above) the probability of not detecting an absolute reduction in mortality in the experimental group of 0.01, 0.02, 0.03, 0.04, and 0.05 is 0.93, 0.89, 0.81, 0.70, and 0.57, respectively. Thus, differences in mortality of the intervention groups of 5% or less are likely to remain undetected with a relatively high probability. Therefore, we have elected to include the dead patients in the comparison between the two intervention groups by assigning the worst possible score to the dead patients. The EQ5D5L is used to estimate QALYs gained in each arm of the trial population. QALYs are estimated by summing up the time spent in each state multiplied by the quality of life attributed to this state. By definition, the value of QALYs is zero from the time of death onwards. Total QALYs will be computed and reported for each patient for the entire duration of the follow-up.

For the study of prognostic markers in the EuroHYP-1 trial, we will apply similar principles as in the Clarithromycin in Patients with Stable Coronary Heart Disease trial (CLARICOR) trial [18]. The study of prognostic markers will not be part of the primary publication.

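### Table 5 gives the worst infarct size as 1 with no unit; read in the plan's ml, patients who die before the scan would score better than average (lesser point: two EQ-5D-5L scales)

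*SAP article*

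**What the plan says.** **Rule for deaths.** The table of amendments (captioned Table 6) states: "The worst possible score is assigned to the dead patients". The overview of changes gives the scope: "assign worst possible score to patients who are not alive at the planned date of measurement of the continuous scores". The Discussion subsection on outcomes measurable only in survivors confirms that infarct size is covered: "three of the original secondary outcomes (NIHSS, EQ-5D-5 L, and infarct size) are only measurable in patients who survive". It explains the purpose: an arm should not look good because its sickest patients died before they could be measured.

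**Value of the worst score.** Only Table 5 gives one. Its NIHSS row reads "0 to 42 Worst = 42", so the label marks the bad end of the scale. The infarct row reads "Brain infarct size at 48 +/-24 hours Worst = 1", with no unit and no range.

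**Infarct scale elsewhere.** The section on power of the original secondary outcomes works in ml: "assuming a minimal relevant difference of 2 ml, a SD of 15 ml". Table 2 has the same SD and difference, and a control mean of 10 ml, marked as assumed.

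**EQ-5D-5L.** Table 5 reads "EQ-5D-5 L score at 91+/-14 days RS: 0 to 100 Worst = 0". The power section reads "assuming a minimal relevant difference of 0.05 points, a SD of 0.40 points", and Table 2 gives a control mean of 0.50.

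**Use in the analysis.** Continuous outcomes go into a general linear model. Infarct size is the fourth secondary outcome in the fixed testing sequence, although the same section also calls it exploratory.

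**The concern.** A general linear model compares means, so the number given to a dead patient enters the arm mean directly. If that number lies on the good side of the survivors' mean, each early death improves the arm's result. That is the distortion the rule was written to prevent.

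Infarct size also stands ahead of EQ-5D-5L and death in the fixed sequence. A distorted infarct result could therefore open or close the tests after it, if testing gets that far.

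The EQ-5D-5L discrepancy is of a different kind. It leaves unclear which EQ-5D-5L quantity Table 5 will report and test.

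**Working it through.** **1. Which scales did the plan use?** Power for two means, two-sided α = 0.05, normal approximation, equal arms assumed: Φ(δ / (SD·√(2/n)) − 1.96), with n per arm.

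| Outcome | Inputs | Calculation | Power | Plan |
|---|---|---|---|---|
| Infarct, N = 800 (Table 2) | δ = 2 ml, SD = 15 ml, n = 400 | Φ(2/1.061 − 1.96) | 0.470 | 0.47 |
| Infarct, N = 250 (power section) | δ = 2 ml, SD = 15 ml, n = 125 | Φ(2/1.897 − 1.96) | 0.183 | 0.18 |
| EQ-5D-5L, N = 800 | δ = 0.05, SD = 0.40, n = 400 | Φ(0.05/0.0283 − 1.96) | 0.424 | 0.42 |

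All three reproduce. The plan's working scales are ml for infarct size and a score with mean 0.50 and SD 0.40 for EQ-5D-5L.

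**2. Where does 1 ml fall?** (1 − 10)/15 = −0.6, that is, 9 ml or 0.6 SD below the assumed control mean. With mean 10 and SD 15 it would be at about the 6th percentile of a lognormal or the 28th of a gamma distribution (shapes assumed). Either way it is on the favourable side.

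**3. Direction and size of the shift.** Let survivors have mean 10 ml in both arms and let a share d die before the scan and be scored 1 ml. The arm mean is 10(1 − d) + 1·d = 10 − 9d, so the arms differ by 9 × (difference in d), in favour of the arm with more deaths. The direction needs only a survivors' mean above 1 ml and unequal early deaths.

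The article gives no death rate before the scan, so these are illustrations:

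- 5% against 2% (assumed): 9.55 against 9.82 ml, a shift of 0.27 ml.
- 10% against 5% (assumed): 9.10 against 9.55 ml, a shift of 0.45 ml.
- The article's day-91 mortalities of 17% and 13.16%, as if every death preceded the scan: 9 × 0.0384 = 0.35 ml.

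The first is 0.27/2 = 14% of the relevant difference. In standard errors it is 0.27/1.061 = 0.25 at N = 800 and 0.27/1.897 = 0.14 at N = 250.

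**4. Sensitivity to the value chosen.** With 5% against 2% dying early and an assumed worst value of w ml, the shift against the arm with more deaths is 0.03 × (w − 10): 2.7 ml for w = 100, 5.7 ml for w = 200 and 8.7 ml for w = 300. Each exceeds the 2 ml relevant difference.

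**5. EQ-5D-5L.** A mean of 0.50 and SD of 0.40 are 0.5% and 0.4% of a 0 to 100 range, so the power inputs are not on Table 5's scale. If Table 5 is the same score multiplied by 100, the inputs become 50, 40 and 5, δ/SD stays at 0.125 and power stays at 0.424.

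**The case against.** Table 5 is a shell for presenting results and does not mention dead patients. The operative rule is the worst possible score, and scoring deaths as 1 ml would contradict both that rule and the table's own label. A slip, or a fraction or rescaled score on which 1 is the maximum, is at least as plausible. This stands, as far as it goes: a reader might infer that the plan deliberately scores the dead as 1 ml, and the documents do not show that. But no section defines another infarct scale, such a scale would conflict with the ml used for power, and no other value is given. The cell is wrong or undefined on any reading.

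The objection on size also stands. At 0.14 to 0.25 standard errors, on invented death rates, the 0.27 ml shift would rarely change a test result. The test counts formally only if the primary outcome and the first three secondaries have all succeeded.

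Three stronger EQ-5D-5L and analysis claims are tempting but unsupported:

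- That the 0.05 difference is too small by a factor of 100, or that the 0.42 power is wrong. The article nowhere pairs 0.05 with the 0 to 100 range, and rescaling leaves power unchanged.
- That 0 is not the worst EQ-5D-5L value because tariffs can go below zero. The article mentions country-specific tariffs but gives no values. Zero is also the same number on both scales and matches the QALY value it assigns after death.
- That infarct size must move to the van Elteren test. As the plan uses it, that test stratifies by nationality only and would lose the seven minimisation factors.

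**Conclusion.** The infarct point holds as a contradiction in a stated figure. The only worst value given is 1 without a unit, and on the plan's ml scale that is a favourable result. Applied literally in the general linear model, it would reward the arm with more deaths before the scan.

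The direction follows from the article's own figures. The size rests on assumed early death rates and equal survivor means, and is probably small: about 0.3 to 0.5 ml in the cases shown. The greater risk is that the value is left to be settled later, because plausible replacements move the comparison by more than the relevant difference.

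The EQ-5D-5L point is a lesser inconsistency of scale between Table 5 and the power inputs. It is not a power error.

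**What to change.** **Infarct size.** Before unblinding, and preferably before any comparison by coded group, replace the 1 in Table 5 by one of:

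- a pre-specified value in ml that is no better than any observed volume, for example the largest volume in the blinded pooled data; or
- a ranking that places deaths before the scan worse than every observed volume, in an analysis that keeps the adjustment for country and the seven minimisation factors.

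State the unit in the table, and add a sensitivity analysis over other worst values.

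**EQ-5D-5L.** Name one score and its range, and use it in both Table 2 and Table 5.

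**Cost.** Two table cells, a sentence or two of text and one extra analysis. The result will depend on the chosen value, and a large value adds variance. For example, with 5% early deaths in both arms, a 2 ml effect in survivors and deaths scored at 100 ml (all assumed), the mean difference is 0.95 × 2 = 1.9 ml and the SD about 24.6 ml, so power at N = 800 is Φ(1.9/1.742 − 1.96) = 0.19 instead of 0.47. The ranking avoids choosing a maximum volume, but its effect measure is no longer in ml and the stated power does not carry over directly.

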#### Multiplicity

We cannot claim a significant beneficial effect of the intervention in the trial if the primary outcome is neutral and a secondary outcome is statistically significant. Therefore, any testing addressing the multiplicity problem must not reduce the power of the test of the primary outcome as compared to the situation where we declare the secondary outcomes exploratory and only test the primary outcome using α = 0.05. Consequently, the primary outcome must be tested initially and using α = 0.05. These requirements may be fulfilled if we use a pre-specified testing sequence (fixed-sequence procedure) where each outcome is tested at α = 0.05 [12]. However, as soon as a non-significant result is obtained, the testing is stopped. However, for exploratory purposes we will calculate the *P* values of the remaining tests and present them. We will use the fixed-sequence procedure starting with the primary outcome and followed by the secondary outcomes, and the exploratory outcomes ordered according to descending power (see Table 2).

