### Statistical analyses

#### Analytical principles

Analyses will be conducted according to the intention-to-treat principle [2] if not otherwise stated.

All primary tests of significance will be two-sided with alpha = 5%. Analyses will be conducted blinded with the two intervention groups coded as, e.g. 0 and 1. Two conclusions will be drawn, one assuming 0 is the intervention group and 1 is the control, and one assuming the opposite. After two abstracts with two conclusions have been written and both accepted by the Steering Group, the code will be broken.

The primary analyses of primary, secondary, and exploratory outcomes will be those of the intention-to-treat population adjusted for the protocol-specified stratification variable and the minimisation variables, and if necessary using data sets generated using multiple imputation.

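### The multiplicity rule places the exploratory outcomes in the fixed sequence by descending power, but neither listed exploratory outcome has a power figure, and the rest of the SAP ends the sequence with the secondary outcomes

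*SAP article*

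**What the plan says.** The Multiplicity section adopts a "pre-specified testing sequence (fixed-sequence procedure) where each outcome is tested at α = 0.05", with the rule that "as soon as a non-significant result is obtained, the testing is stopped". P values for the tests that remain after stopping are still to be presented, for exploratory purposes. The section's last sentence defines the sequence: it starts with the primary outcome, "followed by the secondary outcomes, and the exploratory outcomes ordered according to descending power (see Table 2".

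The section Power of the original secondary outcomes lists two exploratory outcomes: WHODAS 2.0 and number of SAEs per patient. For WHODAS 2.0 it says that "due to difficulties in assessing the clinical meaning, we are not able to calculate the power". For SAEs per patient it says "we cannot calculate power for this outcome. These data will be analysed as an exploratory outcome". Table 2 has six rows, and neither outcome is among them.

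The same section sets out the testing order of the secondary outcomes: NIHSS, proportion with at least one SAE, mRS > 2, infarct size, EQ-5D-5L, death. The exploratory outcomes follow in a separate list that is not called a testing order. The multiplicity row of Table 6 describes the procedure as the primary outcome "followed by the secondary outcomes ordered according to falling power", and gives its purpose as "To keep the family-wise error rate ≤ 0.05". The abstract, the overview of changes and the conclusion of the Discussion describe the same primary-plus-secondary sequence.

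**The concern.** A fixed-sequence procedure needs each test to have a place before the data are seen. Here two outcomes are put into the sequence by a rule that cannot be applied to them. They were made exploratory because no power could be computed, and are then to be ordered by power.

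Their status is also unclear. Under Multiplicity they are steps tested at 0.05 each; everywhere else they lie outside the sequence. The Discussion says that two exploratory outcomes will appear in the main publication, so the analyst needs to know whether a P value below 0.05 for either may be presented as a confirmatory finding or only as a descriptive one.

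**Working it through.** **Inputs.** Two-sided alpha 0.05 (Analytical principles). N = 800 and a type 2 error of 20%, hence primary power 0.80 (abstract, Methods). Effects and SDs for the secondary outcomes come from Table 2 and the section on power. Equal allocation, 400 per arm, is an assumption.

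**1. Table 2 reproduces.** For means, power is Φ(δ / (σ√(2/n)) − 1.96). For proportions, the formula is Φ((d − 1.96√(2p̄(1−p̄)/n)) / √((p₁(1−p₁) + p₂(1−p₂))/n)).

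| Outcome | Inputs | Table 2 | Recomputed |
|---|---|---|---|
| NIHSS | δ 2, SD 5 | 1.00 | 0.9999 |
| At least one SAE | 20% v 10% | 0.98 | 0.978 |
| mRS > 2 | 63% v 55.75% | 0.55 | 0.551 |
| Infarct size | δ 2, SD 15 | 0.47 | 0.470 |
| EQ-5D-5L | δ 0.05, SD 0.40 | 0.42 | 0.424 |
| Death | 17% v 13.16% | 0.33 | 0.329 |
| WHODAS 2.0 | none given | no row | not computable |
| SAEs per patient | none given | no row | not computable |

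The order of the six listed secondary outcomes follows from the Table 2 figures. The last two rows cannot be ranked, because the SAP gives no effect size, SD or rate for either.

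**2. How often the tail is reached.** All seven earlier tests must be significant. If they are independent and the planned effects hold:

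0.80 × 1.00 × 0.98 × 0.55 × 0.47 × 0.42 × 0.33 = 0.028.

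Whatever the correlation, the joint probability cannot exceed the smallest single power, 0.33 (death).

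**3. Error in the tail.** Suppose the tail is reached, both exploratory nulls are true, and the order is chosen after seeing the results. The chance of at least one false claim is then 1 − 0.95² = 0.0975 for independent tests. Simulation with correlated tests gives about 0.095, 0.087 and 0.070 at correlations 0.3, 0.6 and 0.9. With an order fixed beforehand it is 0.05.

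**4. Unconditional size at the planned effects.** Take the tail tests as independent of each other and of the earlier tests. The chance is 0.028 × 0.0975 = 0.003 under independence throughout, and at most 0.33 × 0.0975 = 0.032. To pass 0.05, the tail would have to be reached more than 0.05 / 0.0975 = 51% of the time.

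**5. Infarct size.** The text on power uses 250 participants and obtains 0.18 (recomputed 0.1825), and concludes that the outcome will be exploratory. Table 2 uses 800 and gives 0.47, and the list puts it fourth. So one outcome called exploratory does have a power figure, in fact two. At 0.18 it would rank below death (0.33). If it were left out of the sequence, EQ-5D-5L and death would no longer have to wait for it.

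**The case against.** The best reply is that this is a slip in one trailing clause. The section on power prints the secondary sequence in full and lists the exploratory outcomes apart from it, and four other places describe the procedure as primary plus secondary only. The intended reading is fairly evident. The exploratory list also has a printed order, WHODAS 2.0 then SAEs per patient, and nothing says that the order would be chosen after seeing the data.

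Much of this stands. The intended sequence probably ends with death, and a data-driven order is a possibility left open, not something the SAP plans. But the printed order is never called a testing order, and Multiplicity ties order to power. If the power clause is read as applying only to the secondary outcomes, the exploratory outcomes remain in the sequence with no ordering rule at all. Nor can the clause refer only to descriptive P values, since the section provides for those separately.

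A reader might infer that the family-wise error statement in Table 6 is false. The documents do not support that: Table 6 attaches the aim to the primary and secondary outcomes, whose order is printed. A reader might also take 9.75% as the trial's error rate. It is conditional on seven earlier successes, two true nulls and an order picked afterwards.

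**Conclusion.** The Multiplicity rule is wrong as written. It cannot be carried out for the two listed exploratory outcomes, and it contradicts the SAP's other descriptions of the sequence. Through this clause, no primary or listed secondary test loses its error control.

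The numerical exposure lies in a tail reached about 3% of the time under independence and at most 33% of the time, given the planned effects and equal allocation. Strong control should in principle also hold under larger effects, where the tail would be reached more often, so the theoretical gap remains. In practice the issue is an undefined status for two reported outcomes. The linked conflict over infarct size matters in a different way, because it sits within the sequence, ahead of EQ-5D-5L and death.

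**What to change.** In the last sentence of Multiplicity, delete the reference to the exploratory outcomes. State that the sequence ends with the last secondary outcome in the list under Power of the original secondary outcomes. Report WHODAS 2.0 and number of SAEs per patient with estimates and unadjusted P values, labelled exploratory and outside the sequence.

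In the same edit, settle infarct size: either keep it in the sequence at a fixed position and remove the statement that it is exploratory, or take it out of the list. Its sample size (250 or 800) and power (0.18 or 0.47) should then agree between the text and Table 2. Every outcome will then be either in the sequence at a fixed position or outside it.

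The cost is a few sentences, agreed before the treatment code is broken, with no change to the sample size. For WHODAS 2.0 and SAEs per patient, what is given up is a possible confirmatory claim on outcomes that the SAP already calls exploratory.
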